### Recruitment

All patients presenting to the outpatient unit of the Oral and Maxillofacial Department and fulfilling the enrolment criteria of the study will be recruited. The principal investigator coordinated with each patient to achieve the desired sample size.

## Methods: Assignment of interventions (for controlled trials)

### Allocation: sequence generation

Study participants will be randomized using the SCIENCER application. As a specific age range was chosen for the study, further stratification and subset creation will not be performed.

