### Eligibility criteria

*Inclusion criteria*
1.Patients giving informed written consent.2.Age group 18-40 yrs. The age range is selected to have homogeneity, reduced comorbidities, relevance to the target population and better baseline functionality.3.ASA I and healthy ASA II physical status.4.Patients presenting with impacted mandibular third molars that are indicated for removal.5.Slightly or moderately difficult impacted mandibular third molars, according to the Pederson difficulty index with the difficulty score in the range of 3 to 7.

*Exclusion criteria*
1.Presence of oral mucosal comorbid conditions that may affect salivary inflammatory markers.2.Patients not reporting for follow-up as per study protocol.3.Presence of systemic infections that may alter the levels of serum C-reactive protein.4.Presence of acute infection that necessitates the use of antibiotic therapy.5.Known allergies to drugs under study and local anesthetic agents.6.Patients with a history of xerostomia or hypersalivation.

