### Sample size

The study will be a non-inferiority trial with a continuous outcome.

The sample size was established based on data obtained from a previous study conducted by Salgia et al.
^
11
^ Serum C-reactive protein level was chosen as the primary outcome variable.

Formula using mean difference

$$n1=n2=2\frac{{\left(Z_{\alpha }+Z_{\beta }\right)}^{2}\sigma^{2}}{{\left(\delta \right)}^{2}}$$

$$Z_{\alpha }=1.96\;$$

α = Type I error at 5% at both sides two tailed

Z
_β_ = 0.84 = Power at 80%

Primary Variable = CRP (C-reactive protein) levels

The mean difference after treatment CRP (mean ± SD) for the diclofenac group was 16.305 ± 3.977 (as per the reference article).
^
10
^

Considering 20% clinically relevant margin for aescin = (

16.305∗20)/100=3.26

Sample size:

$$N=n1=n2=2\frac{{\left(1.96+0.84\right)}^{2}{\left(3.977\right)}^{2}}{{\left(3.261\right)}^{2}}=23$$

Assuming 10% dropout = 2

Total sample size required = 23 + 2 = 25 each group.

Thus, a total sample size of 50 subjects presenting with impacted mandibular third molars will be enrolled in the study.

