### Statistical analysis plan

**
*Statistics: outcomes*
**

**
*Statistics: additional analyses*
**

**
*Statistics: analysis population and missing data*
**

*Primary variable*

Inferential statistics will be used to compare the two groups for measurement scores, resulting in their mean change in a primary variable (visual analog scale, facial swelling, mouth opening, salivary prostaglandin E2, serum C-reactive protein) between baseline and end visits.

Baseline variables will be tested for significance in the mean using ANOVA or Kruskal-Wallis test for more than two assessment periods. A post-hoc (Tukey’s or Duncan’s) test will be used to find a significant difference between the two groups for pair-wise comparison.

*Outcome variables*

Outcome variables will be tested for intra-difference in measurement at pre- and post-visits using a paired t-test to determine the mean’s significance. The unpaired t-test for comparison of two groups and ANOVA for comparison of three groups will be used for intergroup differences.

Statistical analysis will be carried out using R-software free version.

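### The age-based reason for not stratifying does not bear on surgical difficulty, and the unadjusted t-test gives up precision that an ANCOVA on data already collected could recover

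*Protocol article*

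**What the plan says.** **Allocation.** The section on sequence generation states "Study participants will be randomized using the SCIENCER application", and then "As a specific age range was chosen for the study, further stratification and subset creation will not be performed". No other reason for declining stratification is given.

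**Who is eligible.** Eligibility criteria set "Age group 18-40 yrs" and admit "Slightly or moderately difficult impacted mandibular third molars, according to the Pederson difficulty index with the difficulty score in the range of 3 to 7". The score is therefore known for every patient before allocation.

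**Design and primary outcome.** Under Sample size: "The study will be a non-inferiority trial with a continuous outcome" and "Serum C-reactive protein level was chosen as the primary outcome variable". The margin is 3.26 (20% of 16.305), the SD 3.977 and the size 25 per group.

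**Analysis.** The Statistical analysis plan section works on mean change between baseline and end visits, and states "The unpaired t-test for comparison of two groups and ANOVA for comparison of three groups will be used for intergroup differences". It names no covariate. Difficulty appears nowhere in the allocation or analysis sections.

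**The concern.** An age limit makes patients alike in age. It does nothing to make the two arms alike in how hard the tooth is to remove. All the clinical and laboratory outcomes (CRP, PGE2, pain, swelling, mouth opening) measure the response to surgery, so difficulty is a plausible prognostic factor. The eligibility limit on the score suggests the authors think so too. The stated reason therefore does not support the decision it is given for.

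The planned t-test then leaves any variation due to difficulty in the error term, along with whatever part of the baseline CRP effect is not removed by analysing change. At stake is power against the 3.26 margin, and how readily this one small trial can be interpreted if the arms turn out visibly different in difficulty.

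**Working it through.** **1. The plan's own figure.** Inputs from Sample size: z values 1.96 and 0.84, SD 3.977, margin 3.261.

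n per group = 2 × (1.96 + 0.84)² × 3.977² / 3.261² = 2 × 7.84 × 15.817 / 10.634 = 23.3. The plan states 23, and 25 after dropout. The figure reproduces.

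**2. Power of the unadjusted t-test.** With the plan's 10% dropout, 25 × 0.9 = 22.5, taken as 22 evaluable per arm. The standard error of the difference is 3.977 × √(2/22) = 1.199, and the noncentrality is 3.261 / 1.199 = 2.72. The noncentral t with 42 degrees of freedom, one-sided 2.5% and a true difference of zero gives power of 75.7%.

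**3. Power after adjustment.** If covariates explain a share R² of the variance, the residual SD is 3.977 × √(1 − R²). R² is not in the protocol, so a range is shown.

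| Assumed R² (baseline CRP and difficulty together) | Residual SD | Power at 22 per arm |
|---|---|---|
| 0 | 3.977 | 76% |
| 10% | 3.773 | 80% |
| 20% | 3.557 | 84% |
| 30% | 3.327 | 89% |

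Charging the two covariates two degrees of freedom changes these by about 0.1 percentage point.

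**4. The part due to difficulty alone.** Assume half the teeth are moderately difficult and that the categories differ by b SD in CRP. Then R² = 0.5 × 0.5 × b² = 0.25 b².

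| Assumed b | R² | Residual SD | Power at 22 per arm |
|---|---|---|---|
| 0.25 | 1.6% | 3.946 | 76.4% |
| 0.5 | 6.25% | 3.851 | 78.3% |

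Most of any larger gain would have to come from baseline CRP.

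**5. Chance imbalance.** Treat the number of moderate teeth in each arm as independent Binomial(25, p). The probability of a gap of 5 or more patients (20 percentage points), in either direction, is 20% at p = 0.5 and 16% at p = 0.3 or 0.7. The value of p is an assumption. A 20-point gap moves the unadjusted difference by 0.20 × b × 3.977:

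- b = 0.25: 0.20, or 6% of the margin
- b = 0.5: 0.40, or 12% of the margin

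For scale, the standard error at 25 per arm is 3.977 × √(2/25) = 1.125, so a shift of 0.40 is about 0.35 of a standard error.

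**The case against.** The strongest reply is that nothing here is invalid. Unstratified randomisation is a legitimate choice in a single-centre trial of 50 patients. The t-test keeps its error rate over repeated randomisations, and chance imbalance is already allowed for in its standard error. That stands in full. A reader might infer that the trial's answer is biased or its type I error inflated; the documents do not support that.

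The protocol also goes some way already. The score is restricted to 3 to 7, and the analysis uses change from baseline. Both reduce the problem. Neither removes it: two categories remain, and preoperative CRP cannot carry the response to an operation not yet performed.

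The effect sizes are assumptions. Nothing in the protocol links difficulty to CRP or gives the share of moderate teeth. It is tempting to assume a 1 SD effect, under which a 20-point gap would shift the difference by 0.80, or 24% of the margin. But that implies difficulty alone explains 25% of the variance, more than the 20% assumed in the middle case for difficulty and baseline CRP together. It should not be used as the headline.

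A reader might also infer badly unequal arms, since no blocking is described. The protocol plans 25 per group, and block details are commonly left to the full protocol. Nor does the protocol give the score that separates the two difficulty categories, so no cut-point can be taken from it.

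Finally, a separate analysis plan may name covariates. This answers an omission, but here the protocol itself states the unpaired t-test and gives the reason for not stratifying.

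**Conclusion.** The point holds as one of efficiency and rationale, not validity. The age range does not justify ignoring surgical difficulty, and the stated t-test forgoes precision available from data the trial already records. The unadjusted plan gives about 76% power at 22 evaluable per arm, a little under the 80% target. Adjusting for baseline CRP and difficulty would bring it to 80% to 89% if together they explain 10% to 30% of the variance. Difficulty alone, at 0.25 to 0.5 SD and an even split, would add less than 3 percentage points.

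These results rest on the protocol's SD applying to the analysed CRP measure, on no true difference between the drugs, and on variance shares that the protocol does not supply. The change is worth making because it costs little, not because the present plan would mislead.

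**What to change.** In the Statistical analysis plan section, replace the unpaired t-test for the primary between-group CRP comparison with a linear model (ANCOVA) containing treatment, baseline CRP and the Pederson difficulty score recorded for eligibility. Fix the model before any unblinded data are seen. Read the adjusted treatment difference and its confidence interval against the 3.26 margin.

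In the sequence generation section, drop age as the reason for not stratifying, or confine it to age. Stratifying allocation by the two Pederson categories is optional. Study status reports a pilot stage, so it is possible only if main-trial randomisation has not begun.

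Cost: one model line, and a protocol amendment approved by the ethics committee and the DSCC as the Protocol amendments section requires. No additional patients, visits or measurements are needed.

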### Allocation concealment mechanism

All the patients will be sequentially numbered for the purpose of allocation concealment.

### Allocation: implementation

The principal investigator will then enrol the participants. The research supervisor allocate the sequence and assign the participants to the intervention.

### Blinding

Trial participants and the principal investigator will be blinded.

### Blinding (masking): emergency unblinding

Unblinding will be performed if a patient reports adverse side effects to the emergency unit during the follow-up period.

### Data collection plan

Demographic, clinical, and laboratory data for each patient will be collected using the JOTFORM application.

### Data collection plan: retention

Telephonic reminders will be administered to each patient, according to the follow-up protocol. The research supervisor will directly dispense medication to the participants to promote retention.

### Data management

Demographic, clinical, and laboratory data will be segregated in the JOTFORM application based on patient codes. The filtered data will be downloaded and stored in an Excel spreadsheet for statistical analysis.

### Statistical analysis plan

**
*Statistics: outcomes*
**

**
*Statistics: additional analyses*
**

**
*Statistics: analysis population and missing data*
**

*Primary variable*

Inferential statistics will be used to compare the two groups for measurement scores, resulting in their mean change in a primary variable (visual analog scale, facial swelling, mouth opening, salivary prostaglandin E2, serum C-reactive protein) between baseline and end visits.

Baseline variables will be tested for significance in the mean using ANOVA or Kruskal-Wallis test for more than two assessment periods. A post-hoc (Tukey’s or Duncan’s) test will be used to find a significant difference between the two groups for pair-wise comparison.

*Outcome variables*

Outcome variables will be tested for intra-difference in measurement at pre- and post-visits using a paired t-test to determine the mean’s significance. The unpaired t-test for comparison of two groups and ANOVA for comparison of three groups will be used for intergroup differences.

Statistical analysis will be carried out using R-software free version.

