## Outcomes

Postoperative sequelae after surgical removal of the impacted mandibular third molar will be estimated by assessing pain, facial swelling, and mouth opening.

Pain: The visual analog scale (VAS)
^
9
^ will be used to assess pain on a scale ranging from 0 to 10. The worst imaginable pain will be graded as 10, and the absence of pain will be graded as 0.

Facial swelling will be measured using a metric tape and standard reference points.
^
7
^ The following reference points will be used for the measurement:
•Soft tissue pogonion - Tragus•The angle of the mandible - Corner of the eye•Corner of mouth - Tragus

Mouth opening: The maximum interincisal distance will be recorded using a metric scale with standardized ruler and a digital Vernier caliper.
^
10
^

Salivary Prostaglandin E2 and serum C-reactive protein levels will be measured by ELISA (enzyme-linked immunosorbent assay (ELISA) preoperatively (T0) on the second postoperative day (T1) and fifth postoperative day (T2).

Patient satisfaction regarding therapy: Study subjects will classify their experience from 1 to 5, where 1 = poor, 2 = fair, 3 = good, 4 = very good, and 5 = excellent.

The need for rescue analgesics will be evaluated by counting the number of tramadol capsules or tablets required by the patient until the fifth postoperative day (T2).

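### The sample size section names serum CRP as the sole primary outcome, but the analysis section lists five primary variables; alpha, margin and power were set for CRP only

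*Protocol article*

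**What the plan says.** In the protocol article, the Sample size section describes one design with one deciding outcome: "The study will be a non-inferiority trial with a continuous outcome", and "Serum C-reactive protein level was chosen as the primary outcome variable". Each input to the calculation belongs to CRP:

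- Type I error: "Type I error at 5% at both sides two tailed", entered as z = 1.96.
- Power: "0.84 = Power at 80"%.
- Mean and SD: the figure "for the diclofenac group was 16.305 ± 3.977 (as per the reference article").
- Margin: "Considering 20% clinically relevant margin for aescin", which gives 3.26.

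The Statistical analysis plan section has a paragraph labelled as the primary variable. It compares the two groups on "their mean change in a primary variable (visual analog scale, facial swelling, mouth opening, salivary prostaglandin E2, serum C-reactive protein") from baseline to the end visit. CRP is the last of five items. Nothing there marks it as different from the other four.

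The Outcomes section labels no outcome as primary or secondary. The first objective is clinical sequelae and the second is the two biomarkers. The conclusions in the Abstract and at the end of the Discussion look forward to findings on postoperative discomfort as well as on the biomarkers.

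**The concern.** The primary outcome fixes which comparison decides the trial. Here two sections of the same article give different answers, and a reader cannot tell from the text which governs.

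This is more than a labelling matter because the design values were worked out for one of the five variables. The other four have no margin and no SD, so the article gives no basis for an 80% power statement about them. If all five are taken as primary, what counts as success depends on whether one is enough or all are needed. The two rules fail in opposite ways: the first inflates the false-positive rate, and the second lowers the chance of success.

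**Working it through.** **1. Reproduce the plan's figure for CRP alone.** Inputs from Sample size: z values 1.96 and 0.84, SD 3.977, margin 20% of 16.305 = 3.261.

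n = 2 × (1.96 + 0.84)² × 3.977² / 3.261² = 23.32 per group. The article prints 23; rounding up gives 24.

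Power at 23 per group (normal approximation): 3.261 / (3.977 × √(2/23)) = 2.781, and Φ(2.781 − 1.96) = 79.4%. At 24 per group it is 81.1%. With CRP as sole primary, the stated 5% and 80% therefore hold, apart from that rounding.

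**2. Five primaries, success on any one, no adjustment.** The calculation assumes no true difference on any of the five (two-sided tests), or aescin exactly at the margin on all five (one-sided tests).

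- Two-sided 5% tests, independent: 1 − 0.95⁵ = 22.6%.
- One-sided 2.5% non-inferiority tests, independent: 1 − 0.975⁵ = 11.9%, against a nominal 2.5%.

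The article gives no correlations, so equal pairwise correlations were assumed and simulated:

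- Correlation 0.5: 18.3% two-sided, 9.1% one-sided.
- Correlation 0.7: about 15% two-sided, 7.4% one-sided.
- Correlation 0.8: 12.7% two-sided, 6.4% one-sided.

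The two-sided figures fit the unpaired t-test in the analysis section and the two-tailed 5% in Sample size. The one-sided figures fit a non-inferiority claim.

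**3. Five primaries, each tested at 0.05/5 = 0.01.** CRP power at 23 per group: Φ(2.781 − 2.576) = 58.1%. For 80% power, 35 per group are needed, or 35/0.9 = 38.9, so 39 with 10% dropout.

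**4. Five primaries, success required on all.** Type I error stays at or below its nominal level. Assuming 80% power for each of the five, joint power is:

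- independent: 0.8⁵ = 33%;
- correlation 0.5: 51%;
- correlation 0.7: 59%.

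The 80% for the four non-CRP variables is an assumption made for this calculation.

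**5. Compare the readings.** CRP only: both 5% and 80% stand. Any of five, unadjusted: the 5% fails. All of five: the 80% fails. Any of five with Bonferroni: error is controlled, but the 80% for CRP fails. No five-primary reading keeps both figures.

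**The case against.** The strongest defence is that the analysis paragraph is loosely worded: it means outcome variables in general, and the explicit statement in Sample size governs. On that reading nothing is wrong with the CRP arithmetic, and both design figures apply. This is a plausible account of the intent, but it does not remove the conflict. The list stands under the primary-variable label, and no other section says which text takes precedence.

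Several stronger inferences are tempting, and the objection to each stands:

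- **That the error rate and the power both fail.** No single success rule makes both fail. Unadjusted any-of-five inflates error but raises the chance of at least one success (above 94% for correlations from 0 to 0.7, with 80% power each). All-of-five loses power but controls error.
- **That there are really seven primary tests, with a 30% error rate.** Outcomes gives three facial reference lines, but the analysis section lists swelling once and does not say that the lines are tested separately. Independence of three distances on one face is also implausible.
- **That the Discussion sets a non-inferiority test for every outcome.** It calls the trial a non-inferiority trial and lists what is compared. It does not specify a test for each.
- **That the primary result could be picked freely after the data are seen.** The published article names CRP in Sample size, so a switch would be visible.
- **That the lack of a multiplicity rule is a separate fault.** Such detail may be in a full protocol or analysis plan not shown. The fault here is what the article states in two incompatible ways.

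**Conclusion.** The article contradicts itself on the primary outcome, and this should be corrected. The 5% and 80% hold together only with CRP as the sole primary.

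The size of the consequence depends on a success rule that the article does not give. For any-of-five it is a family-wise error of up to 22.6% (two-sided 5% tests), or 11.9% against 2.5% (one-sided non-inferiority tests). These are upper figures under independence and fall with positive correlation. For all-of-five it is joint power of about 33% to 59% for correlations from 0 to 0.7, on the assumption that each variable has the 80% power calculated only for CRP.

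The CRP calculation itself is not in dispute on this point.

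**What to change.** In the Statistical analysis plan section:

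- Name the change in serum CRP from T0 to T2 as the single primary variable. This matches Sample size and the baseline-to-end-visit comparison already described in the analysis section.
- State that CRP is the only variable tested for non-inferiority, against the margin given in Sample size.
- List VAS pain, facial swelling, mouth opening and salivary PGE2 as secondary, reported as between-group differences with 95% confidence intervals and without a non-inferiority claim.

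Then align the conclusion in the Abstract, the statement of purpose near the end of the Discussion and its closing conclusion, so that the clinical outcomes are presented as secondary findings.

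Cost: the clinical outcomes can no longer be called primary or non-inferior. The change needs the ethics committee and DSCC approvals set out under Protocol amendments. The sample size does not change. If the sponsor prefers to keep several primaries, each needs its own margin and SD, and the article needs a success rule, an alpha allocation and a new sample size.

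### The 3.26-unit CRP margin equals the intended 20% only if diclofenac averages 16.3 in this trial; the raw-change t-test should give way to a baseline-adjusted comparison with the scale of the margin stated

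*Protocol article*

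**What the plan says.** Protocol article, Sample size: "The study will be a non-inferiority trial with a continuous outcome", and "Serum C-reactive protein level was chosen as the primary outcome variable". The reference input is given as follows: "The mean difference after treatment CRP (mean ± SD) for the diclofenac group was 16.305 ± 3.977 (as per the reference article"). The margin is introduced by "Considering 20% clinically relevant margin for aescin", and 20% of 16.305 is then worked out as 3.26. That figure enters a raw-scale formula with the raw SD of 3.977, giving 23 per arm and 25 after dropout.

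Protocol article, Statistical analysis plan: the arms are compared on "mean change in a primary variable (visual analog scale, facial swelling, mouth opening, salivary prostaglandin E2, serum C-reactive protein) between baseline and end visits". The between-arm test is fixed by this sentence: "The unpaired t-test for comparison of two groups and ANOVA for comparison of three groups will be used for intergroup differences". The section names no margin, confidence limit, ratio or log scale for CRP. No margin for PGE2 appears anywhere.

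**The concern.** The tolerated loss is conceived as a proportion but applied as a number of units borrowed from another study. The two agree at one diclofenac mean only, 16.3. The eligibility criteria and the outcome definitions set no CRP level, and the text does not say which visit 16.305 refers to, or whether it is a post-treatment level or a change.

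The same CRP result can therefore be read in two ways. Suppose the SD is 3.977 with 23 per arm, diclofenac averages 10 and aescin is observed 0.5 higher. The upper 95% limit is 0.5 + 1.96 × 3.977 × √(2/23) = 0.5 + 2.30 = 2.80. That is below 3.26, but above 20% of 10, which is 2.0. The primary conclusion would turn on a choice that the protocol has not made.

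For PGE2 only efficiency is at stake. A raw-scale t-test on a positive concentration loses power if the values are skewed.

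**Working it through.** **Inputs from the Sample size section.** Reference mean 16.305, SD 3.977, margin 20%, two-sided 5% (z = 1.96), power 80% (z = 0.84), 23 evaluable per arm.

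**The plan's own figure.** 0.20 × 16.305 = 3.261. n = 2 × (1.96 + 0.84)² × 3.977² / 3.261² = 23.3, stated as 23. Power at 23 per arm: standard error = 3.977 × √(2/23) = 1.173; 3.261/1.173 − 1.96 = 0.82; Φ(0.82) = 79.4%. The stated size reproduces, on the raw scale.

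**What 3.26 means at other diclofenac means (μ).** 3.261/12 = 27%; 3.261/8.15 = 40%; 3.261/5 = 65%.

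**Chance of passing a drug that is exactly 20% worse**, judged by an upper 95% limit below 3.261. This rule is assumed, because the analysis section gives none, and 16.305 is read as a level.

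P = Φ[(3.261 − 0.2μ)/SE − 1.96]

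- Constant SD: SE = 1.173.
- SD proportional to the mean (CV = 3.977/16.305 = 0.244 in each arm, so the aescin SD is 1.2 times the diclofenac SD): SE = 0.244μ × √((1 + 1.44)/23).

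| μ | 3.261 − 0.2μ | P, constant SD | SE, proportional | P, proportional |
|---|---|---|---|---|
| 16.305 | 0 | 2.5% | 1.295 | 2.5% |
| 12 | 0.861 | 11% | 0.953 | 15% |
| 8.15 | 1.631 | 28% | 0.647 | 71% |

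Simulation of 40,000 log-normal trials with the t-test at the same CV gives about 2.5%, 15% and 69–70%.

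**Power with truly equal drugs, fixed 3.261.** With constant SD it is 79.4% at every mean. With proportional SD, simulation gives about 78% at 16.3, 46% at 24 and 28% at 32.6. The drift in power thus needs the spread to grow with the level. The drift in the table does not.

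**Log scale, limit 1.20.** Log-SD = √ln(1 + 0.244²) = 0.240; SE = 0.240 × √(2/23) = 0.0709; ln 1.20 = 0.182. Power = Φ(0.182/0.0709 − 1.96) = Φ(0.61) = 73%, or about 71% by simulation with the t-test. The error against a true ratio of 1.20 stays at 2.3–2.6% at every mean tried. With an assumed T0 correlation of 0.4, the log-SD becomes 0.240 × √(1 − 0.16) = 0.220 and power 80%. Without that adjustment, 80% needs 28 per arm, or 28/0.9 → 32 with dropout.

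**PGE2.** The document gives no spread and no target effect. For an assumed 40% reduction at 23 per arm, power by raw versus log t-test is about 89% versus 92% at log-SD 0.5, 58% versus 68% at 0.7, and 35% versus 47% at 0.9.

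**The case against.** The Sample size section does not leave the margin relative. It converts 20% to 3.26 and puts that into a raw-scale formula, so sizing and analysis share one scale. Setting an absolute margin as a percentage of a reference mean is common and does not commit a trial to ratios. This stands. Against a fixed 3.26 the test keeps its 2.5% one-sided error at any CRP level. At a diclofenac mean of 8.15, a drug 20% worse differs by 1.63, which lies inside 3.26, so passing it would be correct.

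A reader might infer that the trial's type I error is inflated to 70%, or that non-inferiority is automatic in a low-CRP cohort and nearly out of reach in a high one. The document does not support that. The first needs 20% to be the binding criterion and the SD to be proportional to the mean. The second rests on the same proportionality, which the document neither gives nor rules out, and even at twice the reference mean the power is 28%. A reader might also carry the margin argument over to PGE2, but PGE2 has no margin.

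Nor is a ratio limit of 1.20 plainly the plan's own 20%. If 16.305 is a change, 20% of it is not a 1.20 ratio of concentrations.

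Finally, transforming laboratory markers is often left to a fuller analysis plan. That would answer silence. Here the article names the raw change and the test, and names 20% as the clinically relevant quantity.

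**Conclusion.** The point holds in limited form. 3.26 units represent 20% only at a diclofenac mean of 16.3, and the protocol does not say which of the two is the criterion. Read as 20%, the chance of passing a drug 20% worse rises from 2.5% at the reference mean to 11–15% at 12 and 28–70% at 8.15. The lower figures need only a constant SD of 3.977; the higher ones need spread proportional to level. All assume 23 evaluable per arm, 16.305 as a level, and a decision by the upper 95% limit. Read as a fixed 3.26, no error rate is broken and only the clinical meaning of the margin moves.

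A baseline-adjusted analysis that declares its scale is better than the raw-change t-test and uses data already being collected. For PGE2 the gain is one of efficiency, 3 to 12 percentage points of power over the assumed range.

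**What to change.** In the Statistical analysis plan section, compare log CRP and log PGE2 at the analysis visit between arms with log T0 as covariate. Report the aescin/diclofenac ratio of geometric means with a 95% CI, and keep raw means and SDs as description. No non-inferiority claim attaches to PGE2.

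For CRP, first state in the Sample size section whether 16.305 is a level or a change. Then:

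- **If it is a level and 20% is the criterion:** judge the upper limit of the ratio against 1.20. Restate power as about 71–73% at 23 per arm before T0 adjustment, or about 80% if the T0 correlation on the log scale is 0.4 (assumed).
- **Otherwise:** state 3.26 as the absolute margin, analyse CRP on the raw scale with T0 as covariate, and give the log-scale ratio as a sensitivity analysis.

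Cost: wording in two sections, with no extra visits or assays. The first option lowers the stated power. Reaching 80% without relying on T0 takes 28 evaluable per arm (32 with dropout) instead of 23 (25). A larger CV would raise this steeply: an assumed CV of 0.4 needs 71 per arm. The Study status section describes a pilot stage, so the choice can still be made before any unblinded comparison.
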